# Frailty in older people: Rehabilitation Treatment Research Examining Separate Settings (FORTRESS): protocol for a hybrid type II stepped wedge, cluster, randomised trial

**DOI:** 10.1186/s12877-022-03178-1

**Published:** 2022-06-27

**Keywords:** Frailty, Aged, Implementation, Hospital, Older people, Exercise, Nutrition, Transition, Primary care

## Abstract

**Background:**

Frailty in older people is associated with increased risk of falls, longer length of stay in hospital, increased risk of institutionalisation and death. Frailty can be measured using validated tools. Multi-component frailty interventions are recommended in clinical practice guidelines but are not routinely implemented in clinical practice.

**Methods:**

The Frailty in Older people: Rehabilitation, Treatment, Research Examining Separate Settings (FORTRESS) trial is a multisite, hybrid type II, stepped wedge, cluster, randomised trial with blinded assessment and intention-to-treat analysis being conducted in Australia. The study aims to determine the effectiveness and cost-effectiveness of an embedded individualised multicomponent frailty intervention (commencing in hospital and continuing in the community) on readmissions, frailty and quality of life when compared with usual care. Frail older people admitted to study wards with no significant cognitive impairment, who are expected to return home after discharge, will be eligible to participate. Participants will receive extra sessions of physiotherapy, pharmacy, and dietetics during their admission. A Community Implementation Facilitator will coordinate implementation of the frailty management strategies and primary network liaison. The primary outcome is number of days of non-elective hospital readmissions during 12 month follow-up period. Secondary outcomes include frailty status measured using the FRAIL scale; quality of life measured using the EQ-5D-5L; and time-to-event for readmission and readmission rates. The total cost of delivering the intervention will be assessed, and cost-effectiveness analyses will be conducted. Economic evaluation will include analyses for health outcomes measured in terms of the main clinical outcomes. Implementation outcomes will be collected as part of a process evaluation. Recruitment commenced in 2020 and we are aiming to recruit 732 participants over the three-year duration of the study.

**Discussion:**

This study will reveal whether intervening with frail older people to address factors contributing to frailty can reduce hospital readmissions and improve frailty status and quality of life. If the FORTRESS intervention provides a clinically significant and cost-effective result, it will demonstrate an improved approach to treating frail patients, both in hospital and when they return home.

**Trial Registration:**

Australian New Zealand Clinical Trials Registry (ANZCTR): ACTRN12620000760976p. ANZCTR registered 24 July 2020.

**Supplementary Information:**

The online version contains supplementary material available at 10.1186/s12877-022-03178-1.

## Background

Frailty is a clinical state with multiple causes and contributors in which there is an increase in an older person’s vulnerability for developing increased dependency and/or mortality when exposed to a stressor [1]. The likelihood of being frail increases with age, and frailty is associated with increased risk of falls, longer length of hospital stay, and increased risk of institutionalisation and death [2]. A recent Australian study estimated that 21% of community-dwelling people aged 65 years and over are frail with a higher proportion of women being frail. Approximately 48% of this older population were found to be prefrail [3]. Within hospital settings, Richards et al., [4] reported 49% of adult inpatients were being classified as frail. Prior studies have reported frailty prevalence rates of between 27 and 80% in hospitalised older patients [5, 6].

Frailty is measurable using a range of approaches and validated tools. Two major approaches to identifying frailty are the frailty phenotype and the accumulated deficits model. Frailty phenotype defines frailty as having three or more of: unexplained weight loss, low grip strength, slow walking speed, low physical activity, and self-reported exhaustion [7]. Validated frailty phenotype tools include questionnaires such as the FRAIL Scale [8], and performance-based measures such as the Cardiovascular Health Study (CHS) (often termed “Fried”) Frailty Phenotype [7]. The accumulated deficits model counts diseases, conditions and comorbidities [9, 10]. Accumulation deficit tools measure the number of medical conditions, psychological conditions, physical and cognitive function, and social factors in the Frailty Index [10], or the Clinical Frailty Scale [11] derived from it. Both of these approaches have been shown to be useful for identifying people at high risk of adverse events as a result of their frailty [12]. Whilst many frailty screening instruments are useful in identifying frailty, they do not necessarily direct clinicians to appropriate interventions [13]. The frailty phenotype approach (using the FRAIL Scale or the CHS Frailty phenotype) can give the clinician clear direction for interventions through focussing on the factors that have been identified by the instrument as contributing to frailty. There are generally considered to be four evidence-based areas of intervention for older people with frailty. These are physical exercise, nutritional interventions, multicomponent interventions and individualised care from staff with expertise in geriatric medicine [13–15].

The Asia Pacific Clinical Practice Guidelines for the Management of Frailty [16] provide evidence-based recommendations, including (i) using validated tools to identify frailty, (ii) prescription of physical activity incorporating resistance training, (iii) address polypharmacy, (iv) provide nutritional support, (v) screen for reversible causes of fatigue, and (vi) Vitamin D supplementation. However, guidelines do not implement themselves [17] and there is a need to increase the use of comprehensive, integrated care to better manage patients with frailty, to improve treatment adherence and increase healthy ageing among the older population [18].

The Frailty in Older people: Rehabilitation, Treatment, Research Examining Separate Settings (FORTRESS) study will address this gap through evaluating use of a validated frailty screening tool to guide implementation of an evidence-informed intervention for frailty in the acute hospital setting, with follow up in the community and general practice setting. This pragmatic implementation trial is required to understand effectiveness, cost-effectiveness, adoption, acceptability and adherence of evidence-based frailty identification and management [19].

## Methods

### Design

The FORTRESS trial is a multi-site hybrid type II stepped wedge, cluster randomised trial to be conducted over three years (see Fig. 1). This study protocol is reported in accordance to the Standard Protocol Items: Recommendations for Intervention Trials (SPIRIT) checklist available as supplementary file. The hybrid type II trial approach [20] allows testing of the implementation strategy (Implementation Facilitation [21]) and testing the outcomes of the intervention (screening for frailty and use of appropriate interventions).

**Fig. 1 Fig1:**
[figure not shown]
Overview of the FORTRESS stepped wedge design Participants and sites. SALHN – Southern Adelaide Local Health Network, South Australia. HKH – Hornsby Ku-ring-gai Hospital, New South Wales

The FORTRESS trial builds on previous research conducted by members of the research team. Cameron et al., [22] evaluated the efficacy of a multicomponent interdisciplinary intervention with community dwelling older people after completion of their contact with health services in the Frailty Intervention Trial (FIT). Interventions included multiple sessions of physiotherapy and dietetics, with limited comprehensive geriatric assessment over a period of 12 months. Results of FIT included reduced frailty, improved physical performance, and increased degree of independence for community dwelling older people [22, 23]. Economic evaluation revealed that in very frail older people residing in the community, the multicomponent interdisciplinary intervention was both more effective and less costly than usual care [23, 24].

The protocol for this study has been approved by the Northern Sydney Local Health District Human Research Ethics Committees and is registered at www.ANZCTR.org.au (ACTRN12620000760976p).

The FORTRESS trial will be conducted across six inpatient wards at two different states (Hornsby Ku-ring-gai Hospital, Northern Sydney Local Health District in New South Wales, and Southern Adelaide Local Health Network in South Australia). Older people will be included if they are aged 75 years or older; admitted to the six wards included within the participating local health districts; assessed as frail (score of 3 or above out of 5 on the FRAIL scale [8]); living at home in the community; and score 24 or above out of 30 on the Mini Mental State Exam [25]. People will be excluded if they are admitted to hospital with a new diagnosis of stroke (people with acute stroke are admitted to specialised units in both participating hospitals), have an illness likely to be associated with a life expectancy of < 12 months (assessed on the modified version Illness Severity Rating [20]); are unable to cooperate with the intervention program; were not mobile prior to admission; or reside in a residential aged care home. 

As the trial involves implementation of best-practice guideline recommendations [16] we will use an opt-out approach to participant consent. If people elect to opt-out of the study, they will receive usual care, but will not receive the frailty specific interventions while in hospital and they will not be followed up in the community once discharged.

Partnership with general practices will involve provision of training webinars to the GPs and practice nurses, and GP practice visits for education sessions to practices within the local health networks involved in FORTRESS trial. Education sessions entail primary care frailty management with training on frailty screening, frailty management plans. Within Northern Sydney Health Network, a small group of general practices will be engaged at a one-to-one level to understand the frailty screening process and identify service gaps which can assist in developing co-commissioning strategies. These general practices will provide monthly reporting and feedback for a period of 12 months.

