### Personnel

Two study coordinators (one in NSW and one in SA) will be responsible for project management. Allied health professionals (Implementation clinician, Implementation physiotherapist/Exercise Physiologist, Implementation Pharmacist, Implementation Dietitian) will provide extra sessions of physiotherapy, pharmacy, and dietetics for each ward while the person is an inpatient. A therapist will act as a Community Implementation Facilitator will work with people upon discharge from hospital to assist with implementation of the frailty management strategies and primary network liaison. 

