### Intervention

Patients admitted to the wards taking part in this study are screened for eligibility. Baseline frailty is measured using the FRAIL scale [8] and a score of 3 and above indicates frailty. If the person has been admitted to a ward during the control phase of the research study, they will receive usual care as provided by the ward staff and their general practitioner and other health service providers. Participants admitted to the ward during the intervention phase will receive an individualised intervention designed to treat the identified components of frailty, along with the community implementation visit(s), telephone calls, and support from their general practitioner (GP) once discharged. Additional file 1 outlines the TIDier framework [26] describing the FORTRESS intervention. Intervention is divided into two phases:

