#### Secondary outcomes

Frailty status at baseline, 3 months and 12 months measured using the FRAIL Scale [8].Quality of life at baseline, 3 months and 12 months measured using the EQ-5D-5L [27].Time-to-event of readmission, and readmission rates at 3 months and 12 months.

Baseline measures are assessed by the study Implementation Clinician on the ward at admission. Follow-up outcome assessment will take place via telephone at 3 and 12 months by a health professional masked to group allocation. Each assessment will include administration of the FRAIL Scale to measure frailty and EQ-5D-5L to measure quality of life. Data regarding overnight non-elective hospital readmissions will be obtained from participant self-report, and from public hospital electronic medical records for hospital readmissions.

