### Randomisation procedure

Transition to the intervention phase will be randomised by ward with stratification by site and using minimisation with a random component to optimise baseline and sequential balance. To do this the minimisation algorithm will use anticipated ward characteristics including the type of ward, typical length of stay, high or low tendency to discharge to a day rehabilitation ward rather than home and, where possible, typical readmission rates at that ward.

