### Implementation evaluation

Implementation strategies were informed based on consideration of the Consolidated Framework for Implementation Research (CFIR). The CFIR consists of 40 constructs organised into 5 domains: Intervention Characteristics, Outer Setting, Inner Setting, Characteristics of Individuals, and Process [21]. Implementation facilitation on the wards (during the intervention phase) include staff (employed by the research team) facilitating frailty screening and frailty management plans, multiple education sessions for multi-disciplinary team members, signage and documentation (journey board), and posters within the ward to increase awareness. Implementation facilitation has been shown to enhance uptake and sustainability of evidence based practice [29]. Implementation Facilitation will be evaluated through mixed methods including interviews and assessing levels of engagement. Fidelity to the intervention will be measured by the Community Implementation Facilitator reporting adherence to frailty recommendations and motivation of participants in a checklist. Interviews with hospital staff, study participants and their carers will be conducted following hospital discharge. A process evaluation of implementation strategies will be conducted concurrently to FORTRESS intervention with details to be described in a separate paper.

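### An exclusion defined by the intervention itself, judged after the ward's phase is set, leaves room for different selection in the control and intervention phases

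*Protocol article*

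**What the plan says.** The eligibility paragraph of the protocol article (Methods, after Fig. 1) excludes people who "are unable to cooperate with the intervention program; were not mobile prior to admission; or reside in a residential aged care home". The list appears once and is not limited to a phase. The article gives no rule for judging the cooperation item.

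The Intervention section says "Patients admitted to the wards taking part in this study are screened for eligibility" and only then separates the two conditions: "If the person has been admitted to a ward during the control phase of the research study, they will receive usual care". Under Randomisation procedure, "Transition to the intervention phase will be randomised by ward with stratification by site".

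On who assesses, Secondary outcomes states "Baseline measures are assessed by the study Implementation Clinician on the ward at admission". Personnel places the same role in the delivery team: "Allied health professionals (Implementation clinician, Implementation physiotherapist/Exercise Physiologist, Implementation Pharmacist, Implementation Dietitian) will provide extra sessions". Masking is described for follow-up: "Follow-up outcome assessment will take place via telephone at 3 and 12 months by a health professional masked to group allocation". No masking is stated for screening or baseline.

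Implementation evaluation adds "Implementation facilitation on the wards (during the intervention phase) include staff (employed by the research team) facilitating frailty screening". The Design section also counts frailty screening as part of the intervention being tested.

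**The concern.** In a stepped wedge trial that recruits patients after the wards are randomised, the comparison is fair only if the same kind of patient enters before and after crossover. Most of the entry rules mean the same thing in either phase: age, frailty score, cognition score, new stroke, life expectancy, earlier mobility, residence. The cooperation item does not. On a control-phase ward, staff must imagine a program that is not on offer. After crossover they face real exercise sessions and a home visit, and may find it easier to conclude that a patient cannot manage them. The person who takes the baseline measures is very likely to know which phase the ward is in.

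If the item removes more people after crossover, and those people would have spent more days in hospital, the intervention-phase mean falls without any treatment effect. Intention to treat protects enrolled patients only. The covariables under Statistical analysis (age, sex, frailty, earlier hospitalisations, cognition score, admission diagnosis) may absorb part of the imbalance, but none measures capacity to cooperate.

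**Working it through.** **1. The passages side by side**

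| Question | What the protocol article supports |
|---|---|
| Is the item tied to the program? | Yes, by its wording |
| Is there a program in the control phase? | No, usual care only |
| Is the phase fixed before a patient is screened? | Yes, wards are randomised and patients enter on admission |
| Who takes the frailty score that gates entry? | The Implementation Clinician, listed among the staff giving extra sessions |
| Who applies the cooperation item? | Not stated |
| Is that person masked? | Masking is stated for 3 and 12 months only |
| Is the item applied in one phase only? | No such statement |

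This establishes a route to differential exclusion. It does not show that such exclusion occurs.

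**2. The plan's own figure**

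Sample size gives 732 participants, 35 versus 50 days, 80% power, 5% significance, 10% mortality, 10% dropout and a design effect of 1.75. It gives no standard deviation, so 732 can only be solved backwards (two-sided test and equal groups assumed):

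- effective total = 732 × 0.80 / 1.75 = 334.6, or 167.3 per condition
- SD = 15 / [(1.960 + 0.842) × √(2/167.3)] ≈ 49 days

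This is consistency with an implied SD, not a reproduction. It is used only in step 5.

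**3. Net extra exclusion in the intervention phase**

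Take 50 days as the mean of all otherwise eligible patients. The protocol does not label its two means; reading 50 as control is an assumption. Let a fraction *f* be excluded in the intervention phase but not in control, with *R* times the mean days of the rest. Then 50 = (1 − f)m + fRm, so the remaining mean is m = 50 / [1 + f(R − 1)] and the spurious difference is 50 − m. Both *f* and *R* are assumptions.

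| f | R = 1.3 | R = 1.5 | R = 2 |
|---|---|---|---|
| 2% | 0.30 | 0.50 | 0.98 |
| 5% | 0.74 | 1.22 | 2.38 |
| 10% | 1.46 | 2.38 | 4.55 |
| 15% | 2.15 | 3.49 | 6.52 |

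Examples: 50 − 50/1.006 = 0.30; 50 − 50/1.15 = 6.52. Against the 15-day target the range is 0.30/15 = 2% to 6.52/15 = 43%.

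**4. Exclusion in both phases at different rates**

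Here *r* is the ratio to the overall mean, and remaining mean = (50 − p × 50 × r)/(1 − p).

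- r = 1.5, 2% v 10%: 49.49 − 47.22 = 2.27 days
- r = 1.5, 5% v 15%: 48.68 − 45.59 = 3.10 days (21% of 15)
- r = 1.3, 2% v 10%: 49.69 − 48.33 = 1.36 days
- r = 1.3, 5% v 15%: 49.21 − 47.35 = 1.86 days

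**5. Effect on false-positive risk**

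With SD 49 the standard error is 49 × √(2/167.3) ≈ 5.36 days. Under no true effect, a nominal 5% two-sided test rejects about 5.0% of the time at a bias of 0.30 days, 7.3% at 2.38 and 23% at 6.52. The excess lies on the side favouring the intervention. This is a normal approximation with the plan's design effect, not the planned negative binomial mixed model.

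**The case against.** The strongest reply is that the item is listed once for everyone and that screening is described before the text divides the phases. Whether someone could cooperate can be judged prospectively, for instance from whether they can follow exercise instructions, and that is possible on a control ward. This stands. A reader might infer that the item can be observed only while the program is running, or that sicker patients are removed from the intervention phase alone. The article supports neither.

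Several further points also stand:

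- Being unable is not the same as being reluctant. Reluctance is handled by opt-out consent, which is not confined to one phase.
- Limited life expectancy, low cognition score and earlier immobility are screened out by items that do not mention the program. Few people may be left for the cooperation item to remove, and nothing in the document shows that they would have more readmission days.
- The article says who takes baseline measures, not who applies this exclusion. That the assessor knows the phase is inferred, though the inference is strong for someone who delivers the program on the ward.
- A reader might take facilitated frailty screening to mean that trial screening itself changes at crossover. The article does not say so, and it describes eligibility screening of ward admissions without reference to phase.

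The last line of defence is that a fuller protocol may define how the item is judged. That would help, but the point concerns the stated wording: the item would still refer to the program, which only one phase provides.

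**Conclusion.** The concern holds as a design weakness that permits differential selection by phase, not as proof that such selection takes place. It rests on four features of the text: an exclusion defined by the treatment, entry after the ward's phase is set, a baseline assessor from the intervention team, and masking stated only for follow-up.

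The direction is conditional. The bias favours the intervention if people judged unable to cooperate would have had more readmission days, and reverses if they would have had fewer.

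The size is unknown. The calculated range runs from negligible to close to half of the planned effect, and every exclusion rate and ratio behind it is assumed. It should be read as a reason to close the route, not as an estimate of bias. The item should be changed or standardised; confidence is medium.

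**What to change.** Replace the cooperation item with items that do not refer to the program and can be judged from information available at admission. Record them on one fixed form, by the same procedure, for consecutive admissions in both phases, before any FORTRESS component is offered. State that this trial screening is separate from the ward frailty-screening facilitation described under Implementation evaluation. Keep enrolled people who later cannot take part in the intention-to-treat set. Report exclusions by reason, ward and phase.

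Timing matters. The abstract says recruitment began in 2020, Sample size projects 16 months of enrolment, and the article appeared in June 2022. If recruitment is under way, the item should not be dropped part-way: later periods of a stepped wedge are mostly intervention, so removing it would itself make the populations differ by phase. Instead, standardise how it is applied, record the date of that change, and compare exclusion rates by phase.

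The cost is protocol wording and one data-capture form. Some enrolled intervention participants will adhere less, which dilutes the effect slightly but fits the trial's pragmatic aim.
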